# Efficacy and safety of long-term transcutaneous electroacupuncture versus sham transcutaneous electroacupuncture for delayed gastric emptying after distal gastrectomy: study protocol for a randomized, patient-assessor blinded, controlled trial

**DOI:** 10.1186/s13063-022-06108-z

**Published:** 2022-03-03

**Keywords:** Transcutaneous electroacupuncture, Delayed gastric emptying, Distal gastrectomy, Gastric cancer

## Abstract

**Background:**

Delayed gastric emptying (DGE) after distal gastrectomy impacts patients’ nutritional status and quality of life. The current treatments of DGE seem unsatisfactory or need invasive interventions. It is unknown whether transcutaneous electroacupuncture (TEA) is effective in treating DGE.

**Methods:**

A total of 90 eligible participants who underwent distal gastrectomy will be randomly allocated to either the TEA group (*n* = 60) or the sham transcutaneous electroacupuncture (sham-TEA) group (*n* = 30). Each participant will receive TEA on the bilateral acupoints of Zusanli (ST36) and Neiguan (PC6) for 4 weeks. The primary outcomes will be the residual rates of radioactivity in the stomach by gastric scintigraphy and total response rates. The secondary outcomes will be endoscopic features, autonomic function, nutritional and psychological status, serum examination, and quality of life (QoL). The adverse events will also be reported. The patients will be followed up 1 year after the treatment.

**Discussion:**

The findings of this randomized trial will provide high-quality evidence regarding the efficacy and safety of long-term TEA for treating DGE after distal gastrectomy.

**Trial registration:**

Chinese Clinical Trial Registry ChiCTR2000033965. Registered on 20 June 2020

## Background

Gastric cancer is a common and lethal malignant disease worldwide. Although mortality has decreased substantially, approximately 0.5 million patients die of gastric cancer in China annually [1, 2]. Early diagnosis of gastric cancer and radical gastrectomy improves the prognosis. However, patients have the possibility of rapid or delayed gastric emptying after distal gastrectomy, which impacts their nutritional status and quality of life (QoL) [3, 4]. Specifically, 5–30% of patients develop delayed gastric emptying (DGE) following gastrectomy [5–7]. Postsurgical gastroparesis syndrome (PGS) is also used for this complication [8]. Tomita et al. found that epigastric fullness occurred in 60% of patients who had received pylorus-preserving distal gastrectomy 5 years ago, gastric stasis in the remnant stomach occurred in 40% of these patients, and the gastric emptying function of a liquid and semisolid diet was decreased [9]. Kim et al. showed that over half of postoperative gastric cancer patients had DGE with frequently observed gastric stasis and reflux esophagitis [10]. Jung et al. reported that the incidence of food retention was 55.5%, 31.9%, and 20.9% at 3, 12, and 24 months, respectively, after distal gastrectomy for early gastric cancer patients [11].

Nutritional support, glycemic control, prokinetics, antiemetic medications, endoscopic self-expandable stent placement, and surgical intervention in severe cases are considered to be helpful for DGE patients [12]. Nevertheless, prokinetics lack clinical evidence with possible severe side effects, and secondary surgery is not a preferred choice for postoperative patients.

Acupuncture is widely applied for gastrointestinal motility disorders, and it has been proven effective in DGE in critically ill patients and postoperative gastroparesis syndrome [13]. A meta-analysis suggested that acupuncture with or without medication exhibited a significantly higher total effective rate than control acupuncture [14]. Transcutaneous electroacupuncture (TEA) is modified from traditional acupuncture, and it works on specific acupoints combined with a skin electrode patch instead of acupuncture [15]. In animal models, electroacupuncture (EA) can improve gastric motility, accelerate solid gastric emptying via the vagal mechanism, and ameliorate dyspepsia induced by chemotherapy [16]. A small number of clinical studies proved that TEA could significantly improve gastric emptying in dyspeptic patients [17]. Our previous randomized, controlled, single-center study demonstrated that TEA improved bowel movement and alleviated postoperative ileus after gastrectomy [18].

In this study, we will compare long-term TEA versus sham transcutaneous electroacupuncture (sham-TEA) for DGE after distal gastrectomy. To the best of our knowledge, this is the first randomized, patient-assessor blinded, controlled trial on this subject.

## Methods/design

### Objectives and hypothesis

This study aims to (1) assess the efficacy and safety of long-term TEA for treating DGE after distal gastrectomy and (2) evaluate postgastrectomy patients by endoscopic features, autonomic function, nutritional and psychological status, serum examination, quality of life, and TEA-related adverse events. We hypothesize that TEA can safely improve DGE after distal gastrectomy.

### Study design

The trial will be conducted in the Second Affiliated Hospital of Zhejiang University, School of Medicine. This protocol was approved and monitored by the Medical Ethics Committees of the Second Affiliated Hospital of Zhejiang University, School of Medicine (approval number 2020-454), and Chinese Clinical Trial Registry (approval number ChiCTR2000033965) and will conform to the Declaration of Helsinki, STRICTA and SPIRIT guidelines (Fig. 1). The protocol of this study has been registered in the Chinese Clinical Trial Registry with the number ChiCTR2000033965. All eligible participants will be required to sign an informed consent form before allocation.

**Fig. 1 Fig1:**
[figure not shown]
SPIRIT schedule of enrollment, interventions, and assessments

### Inclusion criteria

All allocated patients met the following inclusion criteria: (1) 18–80 years old, (2) gastric cancer patients considered to have DGE (a half-life gastric emptying by gastric scintigraphy greater than 70 min), (3) within 3–6 months after distal gastrectomy, (4) no gastrointestinal obstruction before surgery, and (5) TNM staging < IV, no distant metastasis.

### Exclusion criteria

Patients who met any of the following criteria were excluded: (1) anastomotic stricture or afferent loop obstruction of the jejunum diagnosed by gastroesophageal radiography, (2) taking drugs such as prokinetics or antidepressant drugs a month prior to surgery or during the trial, (3) severe arrhythmia, (4) tumor recurs during the trial, (5) diabetes mellitus, or (6) mental and physiological illness.

### Dropout criteria

Patients who choose to quit the study voluntarily or have poor compliance during the trial will be considered as having dropped out. Patients can discontinue the trial if a severe adverse effect occurs, and they can adjust the parameters of TEA slightly if the electric current makes them feel uncomfortable during the TEA procedure.

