### Blinding

The researchers who initially applied or taught the TEA or sham-TEA procedures did not participate in the statistical analysis. The patients and statisticians were blinded to the group assignments. If unblinding happens, the participants will be terminated from the trial immediately, and the data will be marked and not included in the final analysis. The researchers will record the reason in CRFs.

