### Sample size

Based on a previous electroacupuncture study on gastric emptying function, the response rate is approximately 50–70% [26–30]; however, the data of sham electroacupuncture are insufficient. Thus, we assumed that the response rates of the TEA group and sham-TEA group were 50% and 20%, respectively. Therefore, Δ is 30%. We estimated the sample size using the following formula:
$$ n=\frac{2{\left({\mu}_{\alpha }+{\mu}_{\beta}\right)}^2P\left(1-P\right)}{\Delta ^2} $$

A sample size of 66 patients will give us a power of 90% (*β* = 0.1) with a two-sided significance level of 0.05 (*α* = 0.05). To compensate for a 20% expulsion rate, a total of 90 patients will be required for the study. We will design a ratio of 2:1 (60 patients in the TEA group, 30 patients in the sham-TEA group) based on the response rates of the two groups.

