### Statistical analysis

Sensitivity analysis will be performed to determine the impact of incomplete records on the results. Intent-to-treat analysis of the results will be performed if there is nonadherence or missing data. Only two data statisticians will have access to the final trial dataset, which will only contain coded data, and they will perform statistical analysis using the SPSS version 22.0 software. Student’s *t* test will be performed to assess the difference in the measurements (the residual rates of radioactivity in the stomach at 45, 60, 75, 90, 105, and 120 min) between the TEA group and the sham-TEA group. Paired Student’s *t* test will be used to compare the differences in serum albumin, NE, TNF-α, IL-1β, IL-6, glucose, LF/HF (sympathovagal ratio), and QoL at baseline and 4 weeks after intervention in each group. The *χ*^2^ test will be used for categorical data such as the PG-SGA, HADS, and adverse events. Univariate and multivariate analyses with multiple linear regression will be used to identify independent predictors of outcome measures. The results will be aggregated as median values. *P* values of < 0.05 will be considered as statistically significant.

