### Quality control

To guarantee the quality of the study, all researchers were well trained in the TEA technique, and the patients or their relatives were taught to implement TEA at home, with the help of a written or electronic user manual. Pictures will be taken and uploaded to our database to check the proper acupoints and frequency of TEA each day. Plans to promote participant retention and complete follow-up are as follows: First, online video calls are available for consultation to resolve any technical issues of TEA implementation and to improve research adherence of the patients. Second, we will confirm the completion of TEA each week. Third, the expenses of round trips to the hospital and relevant examinations will be reimbursed to promote participant retention. Fourth, if the participants discontinue or deviate from the trial, we will collect as much data as possible for further analysis. Researchers will be fully apprised of the inclusion and exclusion criteria, and data will be documented in CRFs. A standard operating procedure will be consistently performed according to the study protocol. Drop-outs and their reasons will be recorded. The Medical Ethics Committees will audit the procedure of the trial, have access to these interim results and make the final decision to terminate the trial.

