Several studies have indicated that TEA could increase vagal activity and suppress sympathetic activity [23, 25, 42, 43]. The LF and HF bands of ECG and the LF/HF ratio can well reflect vagosympathetic activities. Thus, we will assess the sympathetic and parasympathetic activities using ECG.

There are several limitations to our study. First, this trial will be conducted in a single center, so selection bias may exist. We suppose that confounding factors of surgical techniques and postoperative management will be eased if distal gastrectomy is performed by a single medical team. Second, TEA or sham-TEA will be implemented by the patients themselves at home, so the quality of manipulations cannot be guaranteed. Third, symptoms of upper abdominal fullness, early satiety, nausea, and vomiting will not be recorded because most DGE patients present with no specific symptoms [11, 37].

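### Poor compliance with home treatment is classed as dropping out of the study, which conflicts with the promised intent-to-treat analysis and leaves the week-4 scan of non-adherent patients unsecured

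*Protocol article*

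**What the plan says.** Four sections of the protocol article bear on a patient who does not keep up the home sessions.

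- **Dropout criteria:** "Patients who choose to quit the study voluntarily or have poor compliance during the trial will be considered as having dropped out".
- **Sample size:** "To compensate for a 20% expulsion rate, a total of 90 patients will be required for the study".
- **Statistical analysis:** "Intent-to-treat analysis of the results will be performed if there is nonadherence or missing data", and also "Sensitivity analysis will be performed to determine the impact of incomplete records on the results".
- **Quality control:** "if the participants discontinue or deviate from the trial, we will collect as much data as possible for further analysis". This section also provides daily pictures, video calls, reimbursement of travel and examinations, and a weekly check: "we will confirm the completion of TEA each week".

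Treatment is self-applied for 1 h twice daily over 4 weeks (TEA group), which is 2 × 28 = 56 sessions. Clinical outcomes are evaluated after the 4 weeks (Sham-TEA group), with a further assessment at 1 year (Participant timeline). The Discussion concedes that "TEA or sham-TEA will be implemented by the patients themselves at home, so the quality of manipulations cannot be guaranteed".

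**The concern.** Adherence to treatment and availability for outcome assessment are separate matters. A patient may skip many sessions and still attend for scintigraphy. The Dropout criteria merge that patient with one who has left the study, whereas the Statistical analysis section expects to analyse the same patient by intent-to-treat. The plan works only if follow-up is separated from adherence, and the article nowhere separates them.

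Compliance is observed after randomisation and can be influenced by the arm and by lack of benefit. If study status follows compliance, the set of patients with a week-4 outcome may no longer be the randomised set. An intent-to-treat analysis needs an outcome for each patient. A sensitivity analysis can show how much the missing scans might matter, but it cannot supply them. Both primary outcomes, the scintigraphic residual rates and the total response rate, would be exposed.

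**Working it through.** **1. The statements side by side**

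| Section | Status of a poorly adherent patient |
|---|---|
| Dropout criteria | Dropped out, as if withdrawn |
| Sample size | May fall within the 20% expulsion allowance; its make-up is not given |
| Statistical analysis | Covered by intent-to-treat |
| Quality control | Data collected as far as possible; the week-4 scan is not named |
| Blinding | Exclusion of data is stated, but only for unblinded participants |

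The first row cannot be followed together with the third unless dropout is only a reporting label. The word expulsion points away from that reading.

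**2. The plan's own allowance**

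Sample size gives 66 patients, 20% expulsion and a total of 90. Dividing gives 66 / 0.8 = 82.5, so 83; the simple mark-up gives 66 × 1.2 = 79.2, so 80. Neither yields 90. Conversely, 90 × 0.8 = 72, or 48 TEA and 24 sham-TEA at 2:1. The derivation of 66 and 90 is a separate matter; only the 20% is used below.

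**3. What 20% missing outcomes leaves open**

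Inputs from Sample size: 60 and 30 patients, 20% lost, 50% v 20% response (taken here as the rates among those observed). Assumption: the same share is lost in each arm. Counts are expected values.

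- TEA: 12 missing, 48 observed, 24 responders. The rate over all 60 lies between 24/60 = 40% and 36/60 = 60%.
- Sham-TEA: 6 missing, 24 observed, 4.8 responders. The rate over all 30 lies between 4.8/30 = 16% and 10.8/30 = 36%.
- Difference: from 40 − 36 = **4** to 60 − 16 = **44** points.

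In general, with a share m missing in each arm, the range is 30(1 − m) ± 100m points. For m = 0.20 this is 24 ± 20. For m = 0.10 it is 27 ± 10, that is 17 to 37. Each scan kept narrows it.

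**4. Does the loss favour TEA?**

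Let p be the true response rate, and let dr and dn be the shares of responders and non-responders lost. The observed rate is p(1 − dr) / [p(1 − dr) + (1 − p)(1 − dn)]. The documents give no dr or dn; the values here are assumptions. With dr = 0.05 and dn = 0.35:

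- p = 0.20: 0.19 / 0.71 = 26.8%
- p = 0.35: 0.3325 / 0.755 = 44.0%
- p = 0.50: 0.475 / 0.80 = 59.4%

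Loss that is unrelated to outcome leaves the observed rate equal to p. The apparent difference in points is then:

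| True rates, TEA v sham-TEA | Outcome-dependent loss in TEA only | In both arms | In sham-TEA only |
|---|---|---|---|
| 35% v 35% | 44.0 − 35 = +9 | 0 | 35 − 44.0 = −9 |
| 35% v 20% | 44.0 − 20 = 24 | 44.0 − 26.8 = 17 | 35 − 26.8 = 8 |
| 50% v 20% | 59.4 − 20 = 39 | 59.4 − 26.8 = 33 | 50 − 26.8 = 23 |

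Both the direction and the size depend on the assumed pattern.

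**The case against.** The strongest reply is that the protocol already covers these patients. Someone who misses sessions is a deviator, from whom Quality control promises further data. Statistical analysis names nonadherence as a case for intent-to-treat and adds a sensitivity analysis. Where the protocol means removal, it says so: for unblinded participants, "the data will be marked and not included in the final analysis". The Dropout criteria contain no such words, so dropout could be no more than a label for the record of reasons. The compliance threshold and the visit schedule may also stand in the full protocol or in the two figures, which are not shown.

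Much of this stands. A reader might infer that poorly adherent patients lose the week-4 scan or leave the analysis; no section says so. A reader might also infer that the rule biases the trial towards TEA. That requires outcome-dependent loss in TEA alone, or more strongly there than in sham-TEA. Patients are blinded, and sham-TEA is assumed to have more non-responders (80% v 50%), so loss for lack of benefit would be expected there too. Nor does the article say that poor compliance will be the main cause of loss. The missing threshold is not counted here as a fault.

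The conflict in the stated text remains. A best-effort promise does not name the primary assessment or undo the dropout status, and a budget for expulsion supports the reading that such patients are counted as lost.

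**Conclusion.** The point holds as a conflict between stated rules. Dropout criteria and Sample size let a non-adherent patient be treated as lost; Statistical analysis and Quality control imply that the patient is retained. If a site follows the former, patients willing to be assessed may miss the week-4 scintigraphy on which intent-to-treat depends.

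The 4 to 44 point range assumes 20% missing in each arm and 50% v 20% among those observed. It describes any missing outcome, whatever the reason, and so shows what is at stake in keeping scans rather than the effect of this rule. No figure for bias can be given, because the documents do not say whether loss differs by arm or by outcome. The change is worth making because it costs little and a scan not taken at week 4 cannot be recovered.

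**What to change.** Reconcile Dropout criteria and Sample size with Statistical analysis and Quality control by defining two statuses:

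- **(a) Stopped, or poorly adherent to, TEA or sham-TEA.** The patient stays in follow-up, the week-4 scintigraphy and the 1-year assessments are sought as scheduled, and the patient is analysed in the randomised arm.
- **(b) Withdrew consent to further assessment.** This alone is called dropout.

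Name the week-4 scintigraphy in the Quality control sentence on continued data collection. Use the daily pictures and weekly confirmations only to define a supportive per-protocol set, with its cut-off fixed before unblinding. In Sample size, replace the expulsion rate by a rate of lost outcome data. Nothing here alters treatment or the reasons for stopping it.

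The cost is a wording amendment; the assessments are already planned and the relevant examinations reimbursed. The downside is dilution. As an illustration, assume that 20% of TEA patients are non-adherent and respond at the sham rate. The TEA rate becomes 0.8 × 50% + 0.2 × 20% = 44%, and two-sided power at 0.05 with all 60 + 30 patients is 62.0%, against 80.9% with full adherence and 70.9% if 20% of each arm were left out at 50% v 20%. With 10% non-adherent the rate is 47% and power 72.2%. The documents give no adherence rate. The dilution is not created by the amendment, since intent-to-treat under nonadherence is already promised.

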### Recruitment

A total of 90 gastric cancer patients who underwent distal gastrectomy at the gastrointestinal surgery department of the Second Affiliated Hospital of Zhejiang University, School of Medicine, will be included in this study (Fig. 2). Demographic information of the patients will be collected.

**Fig. 2 Fig2:**
[figure not shown]
Flow diagram of the study

All patients will undergo laparoscopic exploration with peritoneal lavage cytology to exclude peritoneal metastasis. The patients will undergo distal gastrectomy for the primary tumor, D2 or D1+ lymph node dissection with truncal vagotomy by a single clinical team. Billroth-I, Billroth-II, or Roux-en-Y reconstruction will be conducted using staplers and suture reinforcement, and Braun anastomosis will not be performed for Billroth-II reconstruction. Patients who have a high risk of recurrence will receive adjuvant chemotherapy.

### Randomization

All eligible patients will be randomly assigned to the TEA group or the sham-TEA group by an allocation ratio of 2:1, and the framework of the trial is assumed as superiority (Fig. 2). The randomization process will be achieved by opening sealed envelopes with computer-generated random numbers by the SPSS 22.0 software. The process will be implemented by a researcher who is not involved in the data collection or analysis.

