Gastric scintigraphy is the gold standard method for the diagnosis of gastroparesis and DGE, but there is no uniform approach due to the differences in the composition, volume, and calories of the meal; the protocol of monitoring; and the analysis of data during the examination [36]. The definition of DGE after gastrectomy is not well addressed or studied. We defined DGE as a half-life of gastric emptying greater than 70 min according to previous studies [9, 37]. Tougas et al. chose a low-fat meal consisting of ^99m^Tc-labeled and scrambled eggs, two slices of bread, strawberry jam (30 g), and water (120 ml); anterior and posterior images were taken at times of 1 min, 60 min, 120 min, and 240 min in all patients, and the distribution of percent gastric residual retention at different time points was analyzed in 123 volunteers [38]. Similarly, Tomita et al. mixed ^99m^Tc tin colloids with a semisolid diet of 200 g of rice gruel with a raw egg. A gastric emptying curve was drawn based on the residual rate of radioactivity in the stomach [9]. Kim et al. used ^99m^Tc tin colloid-raidolabeled boiled eggs, and DGE was defined if a half-time of emptying was over 72 min [37]. In our trial, such a radioisotope method with endoscopy will be used to evaluate the gastric emptying function of these postgastrectomy patients. We will have ^99m^Tc tin colloid mixed with a semisolid diet of 200 g of rice gruel with a boiled egg, which is more in line with the appetites of Chinese people.

Gastric dysfunction after distal gastrectomy may be associated with damage to a gastric pacemaker (located at the junction between the fundus and the body of the greater curvature) and truncal vagotomy [39, 40]. Some studies reported that Roux-en-Y reconstruction could result in Roux-en-Y stasis syndrome due to the destruction of natural small-bowel pacemakers [20–22]. Kim et al. found that DGE was associated with laparoscopic operation and duration of the postoperative period [37]. Chong et al. revealed that gastric emptying within a week after distal gastrectomy was markedly slower in Billroth-I than in Billroth-II, while gastric emptying at 3–6 months showed no difference between the two groups [41]. Accordingly, it is necessary for subgroup analysis of different types of operations.

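### The stated TEA-sham test of residual rates is unadjusted, and no stratified allocation is described, for factors the protocol itself links to emptying; the cost is precision and credibility, not validity

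*Protocol article*

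**What the plan says.** **Allocation.** Under Randomization: "All eligible patients will be randomly assigned to the TEA group or the sham-TEA group by an allocation ratio of 2:1", and "The randomization process will be achieved by opening sealed envelopes with computer-generated random numbers by the SPSS 22.0 software". No stratification factor is named. The Sample size section sets the arms at "60 patients in the TEA group, 30 patients in the sham-TEA group".

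**Comparison.** Under Statistical analysis, the residual rates at the six time points are compared between arms by Student's t test, with no covariate. Categorical data get a chi-squared test. A multiple linear regression is also planned, which "will be used to identify independent predictors of outcome measures"; its covariates are not listed, and it is not presented as the treatment comparison.

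**Prognostic factors.** The Discussion reports that "DGE was associated with laparoscopic operation and duration of the postoperative period" and that Roux-en-Y may lead to a stasis syndrome, and it concludes: "Accordingly, it is necessary for subgroup analysis of different types of operations". The Background reports that "the incidence of food retention was 55.5%, 31.9%, and 20.9% at 3, 12, and 24 months". Patients enter 3 to 6 months after surgery, with any of three reconstructions. The outcome section plans subgroup analyses of response by reconstruction type and by laparoscopic versus open surgery.

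**The concern.** The protocol treats these patient and surgical features as important enough to need their own subgroup analyses, but does not use them where they would help most, in the overall TEA-sham comparison. A subgroup analysis estimates the effect within each stratum. It neither balances the arms nor adjusts the overall estimate. A regression that looks for predictors does not become the treatment comparison by being run on the same data.

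Two things are at stake. First, variation in residual rate that these factors could explain stays in the error term, so the comparison is less precise than it could be. Second, if the 30 sham patients turn out to differ visibly from the TEA patients in, say, Roux-en-Y share, readers will ask whether the result reflects that difference. An adjustment chosen after seeing the imbalance answers this less convincingly than one fixed beforehand.

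**Working it through.** The plan gives no figure for imbalance or for prognostic strength, and it states that there are no pilot data. So there is no figure of its own to reproduce on this point, and prevalence and effect below are assumptions shown over a range.

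**1. Where each factor is used.**
- Reconstruction type: subgroup analysis of response only.
- Laparoscopic or open approach: subgroup analysis only.
- Time since surgery: limited by the 3-6 month entry window, and named in no described analysis.
- The between-arm test of residual rates: none of the three.

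**2. Chance of imbalance.** Inputs are arms of 60 and 30 (Sample size section), or 48 and 24 after that section's 20% loss. For a binary factor with prevalence p, the SD of the between-arm difference in share is sqrt[p(1-p)(1/n1 + 1/n2)].
- p = 1/3 (assumed), 60:30: sqrt(0.2222 × 0.05) = 0.105, or 10.5 points.
- Chance of a gap of 15 points or more: 0.155 by normal approximation (0.15/0.105 = 1.42), 0.18 by exact binomial.
- At 48:24: SD = sqrt(0.2222 × 0.0625) = 0.118; chance 0.20 normal, 0.19 exact.
- At 60:30 with p = 20%, 30% and 50%: exact chance about 0.11, 0.17 and 0.21.

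**3. Size of the shift.** Shift in the response difference = gap × effect of the factor on response.
- A 15-point gap with an effect of 20-30 points (assumed): 0.15 × 0.20 = 3 points to 0.15 × 0.30 = 4.5 points. Over a wider assumed range of 10-40 points, it is 1.5-6 points.
- Standard error of the difference at the plan's 50% and 20%: sqrt(0.25/60 + 0.16/30) = 0.097, or 9.7 points.
- So 3-4.5 points is under half a standard error (4.5/9.7 = 0.46); the extreme of 6 points is 0.62.

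**4. Time since surgery.** Assume a constant rate of decline between the Background's 3- and 12-month figures: ln(55.5/31.9)/9 = 0.062 per month. Retention then falls from 55.5% to 46.1% over the 3-month window, 9.4 points or about 3.1 per month. With entry spread evenly over the window (assumed), the SD of the between-arm difference in mean time is (3/sqrt(12)) × sqrt(1/60 + 1/30) = 0.87 × 0.224 = 0.19 month. That is worth about 0.6 points.

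**5. Unadjusted against adjusted test.** Simulation of a continuous outcome at 60:30, with one binary factor (prevalence 50%, assumed) and two-sided alpha of 0.05:

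| R-squared of factor (assumed) | Unadjusted type I error, given gap ≥ 15 points | Power at 0.65 SD, unadjusted | Power at 0.65 SD, adjusted |
|---|---|---|---|
| 0.05 | 0.06 | 0.82 | 0.83 |
| 0.10 | 0.08 | 0.82 | 0.85 |
| 0.20 | 0.10 | 0.82 | 0.90 |
| 0.30 | 0.14 | 0.82 | 0.93 |

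Over all simulated trials, the unadjusted type I error was about 0.05 at every R-squared. With adjustment it stayed at about 0.05 even among trials with the imbalance.

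**The case against.** The strongest objection is that nothing here is an error. Randomisation makes the unadjusted t test valid, because its standard error already allows for chance imbalance, and step 5 confirms this. A reader might infer that imbalance biases the result. The documents do not support that: a gap of 15 points has well under an even chance, its plausible shift is less than half a standard error, and time imbalance within the entry window is negligible. This part of the objection stands in full.

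The protocol's language is also cautious. It speaks of association for approach and postoperative duration, and of possibility for Roux-en-Y. It reports no Billroth-I/Billroth-II difference at 3-6 months, which is the entry window. Its statements concern who develops delayed emptying, whereas every enrolled patient already has it. A reader might take the factors as proven causes of outcome in this population; that goes beyond the text. The gain from adjustment could therefore be small, as at R-squared 0.05.

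Nor are the factors ignored throughout: reconstruction and approach do appear in planned TEA-sham subgroup comparisons, and the regression might include them.

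Last, a condensed article may leave strata and covariates to a fuller document. It would be wrong to infer that allocation is known to be unstratified; only its description lacks strata. But the t test is a stated method, not a silence, and that is enough for the point.

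**Conclusion.** The point holds as a matter of efficiency and credibility. The main comparison of residual rates is fixed as an unadjusted t test, although the protocol itself identifies features, known at entry, that may explain part of the outcome. Neither the subgroup analyses nor the regression for predictors fills this gap.

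Its size is modest and rests on assumptions: about a 16-18% chance of a gap of 15 points or more at 60:30 in a factor held by one third of patients, and a power gain between about 1 and 11 percentage points as R-squared goes from 0.05 to 0.30. The case rests mainly on Roux-en-Y and surgical approach. Time since surgery adds little through imbalance, but it is the one named factor that no described analysis uses. The change is worth making; leaving it out would not invalidate the trial.

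**What to change.** Before unblinding, replace the t test with a linear model for the residual rates containing treatment, reconstruction (Roux-en-Y versus Billroth), laparoscopic or open approach, and months from surgery to randomisation, and make its treatment term the main comparison.

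For the binary response, prespecify a parsimonious adjusted analysis, for example with Roux-en-Y versus Billroth and approach only. On the plan's rates, 60 × 0.5 + 30 × 0.2 = 36 responders are expected, or 48 × 0.5 + 24 × 0.2 = 28.8 after 20% loss, which will not carry a long covariate list.

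The cost is a few degrees of freedom and slightly more analysis work; all three variables are known at entry. Stratifying the envelopes not yet opened is optional and not part of the required change. It would alter the list during recruitment, and a Roux-en-Y versus Billroth split would not secure sham patients in Billroth-I and Billroth-II separately.
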